### Outcome parameters

The primary endpoint is the cumulative number of new hyperintense lesions identified on T2-weighted brain MRI during the treatment period of 12 months. Additional secondary MRI endpoints comprise the volume of T2 hyperintense lesions and number and volume of contrast-enhancing T1 hypointense lesions, the proportion of patients without any new T1 hypointense and T2 hyperintense lesions, brain atrophy as determined by brain parenchymal fraction and normalized brain volume 18 [19], and changes in brain metabolism (NAA/Cr-quotient) as determined by MR spectroscopy [20,21]. All MRI investigations will be performed using a 3 Tesla MRI scanner (Siemens Healthcare, Erlangen, Germany. Other secondary clinical endpoints include the annualized relapse rate and the proportion of relapse-free patients. A relapse is defined as *de novo* development, aggravation or re-occurrence of a pre-existing neurological abnormality compatible with MS, which lasts a minimum of 24 hours, is separated by at least 30 days from a preceding clinical event and does not occur in the context of fever or infection. Further secondary endpoints are the disease progression as determined by EDSS (evaluated by an independent neurologist) [17], Multiple Sclerosis Functional Composite (MSFC) [22], depression as determined by the Beck Depression Inventory (BDI) [23] and fatigue as determined by the Fatigue Severity Scale (FSS) [24]. Assessment of all clinical and MRI endpoints will be performed by experienced evaluators blinded to both the clinical data and treatment allocation. Peripheral venous blood (serum, heparinized blood for flow cytometry and PBMC isolation) will be sampled prior to and during the intervention to assess the effect on cellular and soluble components of the immune system. In detail, we plan to monitor the Th1/Th2/Th17 balance by concanavalin A stimulation of fresh heparinized blood and determination of cytokines using the cytokine bead array. In fresh heparinized blood, we will measure the frequency of B cells, CD4+ and CD8+ T cell subpopulations, innate immune cells and quantify the activation and homing markers on these cells by multicolor flow cytometry. We will also assess the number of IL-10-producing B cells by stimulation of fresh isolated PBMCs with 0.1 mg/ml CpG ODN2006 for 72 hr and will add phorbol myristate acetate and ionomycin (PMA+iono) for the last 6 hr and brefeldin A for the last 4 hr in order to block cytokine excretion. Detection of IL-10 producing cells is planned as intracellular staining of IL-10 on CD 19 expressing cells by multicolor flow cytometry. Alternatively, IL-10 we will be measured in the culture supernatants by ELISA with aliquots of supernatant taken from cell cultures before the addition of brefeldin A and PMA+iono to the cultures.

### Sample size

Because the present data on the effect of TSO on the development of new T2 hyperintense lesions on brain MRI, which is the primary endpoint of the TRIOMS study, are insufficient for an exact statistical sample size calculation, we have designed the investigation as a pilot study with an *a priori* determined sample size of 25 patients per intervention arm, giving a total of 50 patients. The results of this exploratory analysis could serve as the basis for a further prospective randomized study with a statistically justified sample size.

### Blinding

Both the patients and all study personnel will remain blinded throughout the complete treatment period of 12 months. Treatment allocations will only be disclosed after the final database lock or in case of emergency. The active study therapy and placebo bottles will be supplied by OVAMED GmbH and labeling of bottles and randomization of patients will be performed in the central pharmacy of the Charité - Universitätsmedizin Berlin. The patients will mainly be attended to by a “treating physician”, responsible for evaluating the inclusion or exclusion criteria, adverse events, relapses, side effects and so on. All neurological examinations will be performed by an independent “evaluating physician”. To separate the physicians’ function in a threating and an evaluating position in order to prevent unblinding is necessary because patients under therapy with TSO commonly report gastrointestinal side effects that may point the physician to the verum therapy. Similarly, evaluation of all other paraclinical parameters, including MRI, will be conducted by independent examiners. Any patient-related crosstalk between treating and evaluating physicians or examiners will be prohibited unless required for safety reasons. A simple unblinding procedure has been designed, which allows for rapid unblinding of a patient in case of a medical necessity. If the patient is unblinded, he or she will be automatically excluded from the study.

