## Background

Multiple sclerosis (MS) is a chronic inflammatory disease of the central nervous system (CNS), whose incidence has increased over recent decades [1] and which features a specific geographical distribution with higher incidence rates in developed Western nations [2,3]. Although the etiology remains unclear, MS is widely assumed to be an autoimmune disease, in which both genetic susceptibility and environmental factors play a role [4]. In 1966, Leibowitz *et al.* first suggested that MS might be associated with high sanitation standards during childhood [5], and subsequent epidemiological surveys have confirmed high MS prevalence in regions where such standards are the norm [6]. Beneficial immunomodulation by helminths in humans has been demonstrated in an observational study of relapsing-remitting (RR) MS patients with asymptomatic, community-acquired gastrointestinal infections [7]. Compared with uninfected MS patients, parasite-infected patients showed a significantly lower number of exacerbations, stable disability scores, and fewer new T2 and gadolinium enhancing (Gd+) lesions in brain magnetic resonance imaging (MRI). Consequently, new treatment paradigms based on the hygiene hypothesis were developed for autoimmune diseases, including the administering of non-pathogenic live microorganisms. The first clinical trials using *Trichuris suis* ova (TSO), a pig whipworm that is non-pathogenic in humans, in autoimmune diseases, such as inflammatory bowel disease, showed good tolerability and a striking suppressive effect on the autoimmune response [8]. Recently, Fleming *et al.* completed a phase I controlled trial that showed significant reduction of disease activity in RRMS patients under treatment with TSO [9]. We have also analyzed the effects of TSO in four patients with secondary progressive MS and observed a slight down-regulation of the Th1-associated cytokine pattern, especially interleukin (IL)-2, with a temporary increase of Th2-associated cytokines, such as IL-4. Furthermore, mild eosinophilia and changes in CD4+ and CD8+ T cells and natural killer (NK) CD56 bright cell numbers were evident [10].

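### Relapse is assigned to the treating physician, who also takes the side-effect history, although the article promises that all clinical endpoints are assessed by evaluators blinded to clinical data

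*Protocol article*

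**What the plan says.** **Outcome parameters (protocol article).** Relapse yields two endpoints: "Other secondary clinical endpoints include the annualized relapse rate and the proportion of relapse-free patients". Later in the same section, with no exception for relapse, the article states: "Assessment of all clinical and MRI endpoints will be performed by experienced evaluators blinded to both the clinical data and treatment allocation". A relapse is a new, worsening or recurring neurological abnormality in keeping with MS, "which lasts a minimum of 24 hours, is separated by at least 30 days from a preceding clinical event and does not occur" alongside fever or infection. For disability, independence is stated outright: "the disease progression as determined by EDSS (evaluated by an independent neurologist").

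**Blinding (protocol article).** The treating physician is "responsible for evaluating the inclusion or exclusion criteria, adverse events, relapses, side effects and so on". The other role is defined by examination: "All neurological examinations will be performed by an independent" evaluating physician. The reason given for having two physicians is that "patients under therapy with TSO commonly report gastrointestinal side effects that may point the physician to the verum therapy". The same section keeps all study personnel blinded to allocation for the 12 treatment months. It bars the two physicians from discussing a patient unless safety requires it, and gives MRI reading to independent examiners.

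**The concern.** The two-physician arrangement exists to keep people who hear about side effects away from outcome assessment. Relapse is an outcome, yet the article names the treating physician as the one who evaluates it. That physician also records the complaints that the article fears could reveal active treatment.

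At stake is the credibility of the two relapse endpoints. Whether an episode counts involves judgement: whether the abnormality is compatible with MS, whether it lasted long enough, and whether fever or infection accounts for it. If the person judging has formed a view of the allocation from side effects, relapses could be classified differently in the two arms even though no one has been told the allocation. An episode that was never examined by the independent physician at the time may be impossible to re-adjudicate later.

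**Working it through.** No sample size, event count or error rate enters this point, so there is nothing to compute. The check is a comparison of the article's own statements.

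1. **Is relapse a clinical endpoint?** Yes. Outcome parameters names the annualized relapse rate and the relapse-free proportion as secondary clinical endpoints.
2. **What is promised for clinical endpoints?** The same section promises assessors blinded in two respects, to clinical data and to allocation, and applies this to all clinical and MRI endpoints.
3. **Who evaluates relapse?** The Blinding section gives it to the treating physician, in one list with adverse events and side effects.
4. **Is that person blinded to clinical data?** No. Evaluating adverse events and side effects means handling clinical data. Steps 2 and 3 therefore contradict each other.
5. **Is that person blinded to allocation?** Formally, yes, like all study personnel. There is no literal contradiction here. But the Blinding section itself says that gastrointestinal complaints may point to active treatment, and Randomization and interventions adds telephone check-ups after dispensations without a visit because such complaints were frequent in earlier studies. The risk of functional unblinding is the article's own.
6. **Does the evaluating physician's examination close the gap?** Not as written. That physician does all neurological examinations, but the relapse definition requires neither an examination finding nor that physician's confirmation. Discussion between the two physicians is barred except for safety, and no hand-over for relapse decisions is described. Treatment-period visits fall at months 3, 6, 9 and 12, three months apart, while a qualifying episode need last only 24 hours. An episode could therefore resolve before a scheduled examination.
7. **How far does it reach?** The primary endpoint is a count of new T2 lesions read by independent examiners. EDSS is scored by an independent neurologist. That leaves the two relapse endpoints.

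**The case against.** The strongest reply has four parts.

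- **The treating physician is blinded.** This is true for allocation, and it limits the point: a reader might infer that relapses are assessed open-label, and the article does not support that. The promise about clinical data is still not met.
- **Blinding to clinical data cannot apply literally to relapse.** Nobody can judge a 24-hour duration, a 30-day gap or the absence of fever and infection without some history. This stands. It means that the assessor must receive a defined minimum of history. It does not mean that the assessor must be the person who collects the side-effect reports.
- **The independent physician supplies the examination findings, and a confirmation step may be in the full protocol.** Details are commonly left to that document, and a missing confirmation procedure would not by itself be a fault. The fault here is a role that the article does assign, in conflict with a safeguard that it also states.
- **The endpoints are secondary and exploratory.** This is correct. Sample size describes a pilot, and Statistical methods treats all P-values as exploratory and disclaims adequate power. That lowers the weight of the point without removing the contradiction. Sample size also says that the results could serve as the basis for a further trial, so the relapse data may be used again.

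**Conclusion.** The point holds as an internal contradiction with a limited reach. The article promises assessors blinded to clinical data for all clinical endpoints, and assigns relapse to a physician who cannot be blinded in that way. It adds a risk of functional unblinding that the article itself recognises. Two exploratory secondary endpoints are affected. It is worth correcting, but it does not threaten the primary MRI comparison or EDSS.

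The conclusion rests on reading the treating physician's responsibility for relapses as including the decision used in the analysis. The article describes no other decision-maker.

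A reader might go further in three ways that the document does not support:

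- **That the bias favours TSO, or has a known size.** The article gives no relapse rate and no misclassification rate. Any figure would only return the assumed inputs.
- **That eosinophil counts are a second route to unblinding.** Background reports "mild eosinophilia and changes in CD4+ and CD8+ T cells" in four patients with secondary progressive MS. Table 2 lists a safety laboratory without saying whether it includes a differential count or who sees the result.
- **That gut symptoms under TSO would be treated as an infection that disqualifies a relapse.** Nothing in the article says so.

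**What to change.** Reconcile Outcome parameters with Blinding as follows.

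- **Decision.** The evaluating physician decides, for the endpoints, whether an event meets the relapse definition in Outcome parameters. Only events so classified enter the relapse rate and the relapse-free proportion.
- **Referral.** Every suspected relapse that a patient reports goes to an unscheduled visit with the evaluating physician. Randomization and interventions already allows such visits. The treating physician does not pre-screen; otherwise selective discounting could simply move one step earlier.
- **Hand-over.** A short standard form gives the evaluating physician only the onset and duration of the neurological symptoms and whether fever or infection was present. It carries no gastrointestinal or other side-effect information. The form should be named as a permitted exception to the ban on discussion between the two physicians.
- **Unchanged.** Clinical care of relapses, and the evaluation of adverse events, stay with the treating physician. Laboratory reporting is not altered.

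The cost is some additional evaluator examinations, one form and revised role wording. No new staff are needed, because the evaluating physician already exists and already performs all neurological examinations.

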### Randomization and interventions

The eligibility of patients will be determined at the screening visit. At the baseline visit, patients who qualified for participation in the study will be stratified according to gender and disease course (RRMS/CIS) and randomized 1:1 into the two intervention groups. One group will receive TSO 2,500 eggs orally every 14 days, the other a placebo suspension orally every 14 days. Visits will be carried out after 3, 6, 9 and 12 months (Table 2). To ensure reliable monitoring of tolerability, telephone check-ups are planned after every dispensation if a patient does not visit the study center, because prior studies have shown frequent gastrointestinal adverse events or symptoms after therapy with TSO [18]. Optional follow-up visits will be offered at 15 and 18 months after randomization. If necessary, additional unscheduled visits can be performed at any time.

**Table 2 T2:** Time schedule of regular study visits

	**Screening**	**Random (month 0)**	**Tel.V1 -6 (week 0, 2, 4, 6, 8, 10, 16, 20, 28, 32, 40, 44) ± 3 days**	**V1 (month 3) ± 10 days**	**V2 (month 6) ± 10 days**	**V3 (month 9) ± 10 days**	**V4 (month 12) ± 10 days**	**V5 (month 15) ± 10 days **** *(optional)* **	**V6 (month 18) ± 10 days **** *(optional)* **
Informed consent	x								
In/exclusion criteria	x	x							
Randomization		x							
Demographic data	x								
Pregnancy test	x								
Confirmation of MS diagnosis	x								
Relapse history	x	x		x	x	x	x	x	x
Medical history	x	x		x	x	x	x	x	x
Physical examination	x			x	x	x	x		x
Vital signs	x	x		x	x	x	x		x
Weight	x						x		x
MSFC	x						x		x
EDSS	x		x	x	x	x	x		x
Safety lab	x			x	x	x	x		x
Immunological sampling		x		x	x	x	x		x
MRI	x				x	x	x	optional	optional
AE/SAE				x	x	x	x	x	x
Questionnaires (fatigue, depression)	x	x			x	x	x	x	x
Drug supply		x	x	x	x	x			
Drug account					x		x		

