### Statistical methods

Endpoints will be evaluated by both intention-to-treat- and per-protocol-analyses. Statistical tests and presentation will be appropriate to the scaling and distribution of the respective variables. Because TRIOMS is planned as a pilot study, there is a statistical analysis of endpoints, but *P*-values will be considered exploratively without confirming generalization of hypotheses about the study treatments. Due to the restricted sample size of the pilot study, sufficiently powerful statistical analysis is not possible. The primary end point will be analyzed using Fisher’s exact test. Secondary endpoints will be analyzed non-parametrically using Mann–Whitney-U-test, due to the small sample size and possible deviations from normality. Frequencies will be compared with the Fisher’s exact test.Because of the exploratory character of the analysis, alpha-adjusting will not be performed. The test level for statistical significance of differences between both treatment arms is defined as *P* = 0.05 (two-sided) for all tests. For statistical analyses use of the following software is planned: SAS, version 9.4 (SAS Institute Inc. Cary, North Carolina, US); SPSS, version 20 (IBM, Armonk, New York, US) and StatXact 6 from CYTEL (Cytel Inc., Cambridge, Massachusetts, US).

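### The rule that an unblinded patient is automatically excluded from the study conflicts with, or at best undermines, the promised intention-to-treat analysis

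*Protocol article*

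**What the plan says.** In the protocol article, the Blinding section allows the code to be broken before the end of the trial only in an emergency: "Treatment allocations will only be disclosed after the final database lock or in case of emergency". It describes a procedure "which allows for rapid unblinding of a patient in case of a medical necessity". The consequence is then stated without exception: "If the patient is unblinded, he or she will be automatically excluded from the study".

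The Statistical methods section commits to two analyses: "Endpoints will be evaluated by both intention-to-treat- and per-protocol-analyses".

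The primary endpoint in Outcome parameters is the "cumulative number of new hyperintense lesions identified on T2-weighted brain MRI during the treatment period of 12 months". Table 2 schedules the on-treatment MRI scans at months 6, 9 and 12, and relapse history and AE/SAE recording at every visit from month 3 onwards. The Sample size section fixes a "sample size of 25 patients per intervention arm, giving a total of 50 patients".

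**The concern.** An intention-to-treat analysis keeps every randomised patient in the allocated arm and needs outcome follow-up to continue whatever happens after randomisation. The Blinding rule takes patients out because of something that happens after randomisation. It does not say whether they leave study medication, the visits, the per-protocol set or every analysis.

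The loss may also be uneven between arms. The Blinding section itself expects that "patients under therapy with TSO commonly report gastrointestinal side effects that may point the physician to the verum therapy". If tolerability problems lead to code breaks, TSO patients could be excluded more often than placebo patients.

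Two things are at stake. The first is the comparison of lesions and relapses between the randomised groups, which is meant to inform a later trial. The second is safety. The abstract lists safety and tolerability among the things to be assessed, and the rule would end scheduled adverse-event recording in patients with a medical problem serious enough to break the code.

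**Working it through.** The article gives no figure to reproduce here. The check is one of consistency, followed by a statement of scale.

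**Two readings of the rule**

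| Reading of exclusion | Effect on intention-to-treat | Effect on data |
|---|---|---|
| Removed from the analysis | Direct contradiction: a randomised patient is left out | Data collected are not used |
| Withdrawn from participation, earlier data kept | No literal contradiction over the analysis set | Later MRI, relapse and scheduled AE/SAE data are never collected |

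Under the second reading, a patient excluded at month 4 has no scheduled MRI after screening, because the first on-treatment scan is at month 6. A patient excluded at month 7 has one of three. The 12-month cumulative count is then missing or truncated by the protocol's own rule. An analysis plan can keep such a patient in the set but cannot recover scans that were not made.

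**Share of the trial.** With 25 patients per arm and 50 in total (2 × 25 = 50), one patient is 1/25 = 4% of an arm and 1/50 = 2% of the trial. Three in one arm are 3/25 = 12% of that arm.

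**Possible bias if patients are removed.** These figures are illustrative. Assume that 70% of patients in both arms have at least one new lesion, that is 0.70 × 25 = 17.5 expected per arm, and that *k* patients are removed from the TSO arm only. The 70% and the values of *k* are assumptions and are not in the article.

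| Patients removed | TSO proportion | k = 1 | k = 2 | k = 3 |
|---|---|---|---|---|
| All with lesions | (17.5 − k)/(25 − k) | −1.2 points | −2.6 points | −4.1 points |
| In proportion (unrelated to outcome) | (17.5 − 0.7k)/(25 − k) | 0 | 0 | 0 |
| All without lesions | 17.5/(25 − k) | +2.9 points | +6.1 points | +9.5 points |

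Each entry is the proportion minus 0.70. For example, 16.5/24 = 0.6875 and 17.5/24 = 0.729. The bias can go either way or be nil.

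**Effect on the P-value.** Fisher's exact test is the planned primary test. Applying it to the proportion with at least one new lesion is an assumption. Take placebo 20/25 with lesions and remove *k* TSO patients, all with lesions:

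| TSO before removal | k = 0 | k = 1 | k = 2 | k = 3 |
|---|---|---|---|---|
| 13/25 | 0.072 | 0.038 | 0.034 | 0.018 |
| 14/25 | 0.128 | 0.072 | 0.066 | 0.037 |
| 15/25 | 0.217 | 0.128 | 0.120 | 0.116 |

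One exclusion can cross 0.05 in some tables and not in others, and only when selection is on the outcome.

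**Lesion counts.** In 20,000 simulated arms of 25 negative binomial counts (assumed mean 5, size 1), the mean after removing two patients, relative to the full arm, is 1.00 if they are chosen at random, about 0.93 to 0.94 if chosen from the upper half, and 0.78 if they are the two highest. Under the same assumptions and with no exclusions, chance alone gives a 95% range for the ratio of arm means of about 0.53 to 1.84.

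**The case against.** The strongest reply is that the Blinding section is about conduct and the Statistical methods section about analysis. A patient can leave the study and still be analysed as randomised with the data collected up to then. Analysis sets and the handling of withdrawals are commonly left to a fuller protocol or analysis plan, which is not shown. The trial is a declared pilot with exploratory P-values, and emergency code breaks may be rare.

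Much of this stands. A reader might infer three stronger things that the article does not support:

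- *That the rule and intention-to-treat can never both hold.* This is strictly true only if exclusion means removal from the analysis. Under the withdrawal reading the harm is missing data.
- *That code breaks will follow serious adverse events or severe disease activity, and so remove patients with many lesions.* The article names only medical necessity and emergency. The one difference between arms that it supports is in tolerability, which need not track lesion count.
- *That a spurious ratio of 0.93 to 0.78 will arise without a treatment effect.* That needs assumed counts, exclusions in one arm only, and selection of patients with high counts. Random removal gives 1.00. The article also does not say that follow-up of an ongoing adverse event stops or that collected data are discarded.

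Two parts of the reply fail. The point concerns a rule that is printed, not a definition that is absent. And no analysis plan can restore follow-up that the rule has ended. Protecting the blind does not require exclusion either, because the article already separates treating from evaluating physicians, has MRI evaluated independently, and prohibits crosstalk between them except where safety requires it.

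**Conclusion.** The concern holds as a fault in a stated rule, of moderate severity. As written, the rule either contradicts the intention-to-treat analysis or ends the follow-up on which that analysis depends. The document does not say which.

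The size and direction of any bias cannot be derived, since there is no unblinding rate, no split by arm and no stated link to lesion count. What can be said is that each case is 4% of an arm, that bias is nil if exclusion is unrelated to outcome, and that with 25 per arm one to three cases could matter if it is related. The percentages, P-values and ratios above rest on assumed inputs and show scale only.

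The exploratory status of the trial and the probable rarity of code breaks keep this below a critical fault. They do not remove it, because the estimates are meant to feed a further trial and safety is a stated aim.

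**What to change.** Replace the sentence in Blinding with wording to this effect: a patient whose allocation is disclosed continues scheduled visits, MRI and AE/SAE recording where consent allows, is analysed in the allocated arm in the intention-to-treat set, and is left out of the per-protocol set only. Add that the evaluating physician and the MRI readers are not told of the code break, and that the number, timing and reasons of unblindings are reported by arm.

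Whether study medication continues after unblinding is a clinical matter and is not addressed here.

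The cost is a short protocol change. The visits and scans are already in Table 2, and separate evaluators are already planned. The change should precede the first code break, because follow-up lost under the present rule cannot be recovered.
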